### 4.3 Exclusion criteria

Potential participants undergoing an abortion at the abortion clinic will be excluded from study participation if they are infected with HIV, hepatitis B or other blood borne infectious diseases. This is an exclusion criteria set by the abortion clinic for participation in any research with residual tissues for security reasons.

Additionally, samples retrospectively collected at the Erasmus MC for which no explicit informed consent is available, will be excluded if they have not seen a (research) nurse during their pregnancy to discuss the potential use of residual tissue or when there is known objection against use of material for research purposes in the Erasmus MC 'database bezwaren'.

### 4.4 Sample size calculation

Our primary outcomes are DMRs in placental DNA between different trimesters. Since no placental methylation studies have been performed using MeD-seq, it is unknown what the methylation profiles will look like.

Power calculations are therefore not possible. Based on previous experiments to generate reference profiles using MeD-seq in other tissues, the number of reliable DMRs stabilizes when having a sample size of a minimum of 10 samples. Therefore, we aim to include at least 10 different samples per trimester both retrospectively and prospectively.

### 4.5 (Planned) start date

We plan to start right after METC approval.

### 4.6 (Planned) end data

We expect to finish within 1.5 years after the start of this study.

## 5. Methods

- 5.1 *Please describe how you do conduct research and which methods are used, e.g. questionnaires, human material collection, extraction of data from medical records, analysis of images, the use of an app/medical device/diagnostic test, clinical tests to be performed, etc. Include information on frequency, duration, volumes, if a Data Management Plan is available (then please upload DMP).*

Placenta samples from all three trimesters from both complicated and uncomplicated pregnancies will be obtained in multiple ways as described earlier: via the Fetal Biobank Amsterdam (retrospectively), abortion clinics (prospectively) and the Erasmus MC (both retrospectively and prospectively). After sample collection, DNA will be isolated from placental biopsies. MeD-seq technology will be used to investigate DNA methylation profiles between different trimesters in both complicated and uncomplicated pregnancies. Custom Python scripts will be used to process the acquired DNA methylation profiles. Raw data files (fastq) will be filtered to be able to distinguish methylation data from background data and will be mapped to the human genome (hg38) using bowtie. To subsequently analyse DMRs, we will generate both regional (promoter, gene body and cytosine-phosphate-guanine (CpG) Island regions) as genome-wide methylation scores. For the genome-wide analysis, a sliding window technique will be used to detect DMRs. The Chi-squared test will be used for statistical testing with either the False Discovery Rate (FDR) or Bonferroni correction for multiple testing. A FDR or Bonferroni adjusted p-value <0.05 will be considered significant. After DMRs are determined, Z-score transformation of the read count data will be applied for unsupervised hierarchical clustering analysis. Pathway analyses will be performed using <http://geneontology.org>.

- 5.2 *Standard clinical care versus extra for research:  
Indicate which of the methods are part of standard clinical care and which tests and/or visits are extra for research purposes i.e. not standard clinical care.*

Since only residual tissues will be used, participants will not undergo any additional procedures. The placentas would otherwise be discarded. Sample collection and MeD-seq is only for research purposes.

- 5.3 *Please describe the burden and risks associated with participation, e.g. the amount and number of blood samples, biopsies, liquor, hair, urine, nails, saliva etc., the number of site visits, physical examinations or other tests, questionnaires or diaries that have to be filled out, physical and psychological discomfort associated with participation.*

Not applicable since participants will not undergo any additional procedures.

- 5.4 *A risk-benefit analysis must be given, if applicable.  
If a non-therapeutic study is carried out with minors or incapacitated subjects, it should be specified whether the risks are negligible and the burden minimal and why the study is group related*

*(i.e., study can only be done using these patients groups).*

The participants will not personally benefit from the study. However, the obtained information can lead to a better understanding of placental development in normal pregnancies. In the future, our aim is to use this information to be able to understand normal placental development over the course of pregnancy, unravel underlying pathophysiology of placenta-related complications and to develop biomarkers to predict disease risks at an early stage of pregnancy. Participants will not undergo any additional risks related to this study.

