### Secondary objectives:

- 2) Identify underlying genes or genetic pathways related to identified DMRs involved in (ab)normal placental development.
- 3) Identify placental DNA methylation profiles to specifically distinguish the placental derived fraction from the maternal one in total cfDNA in the maternal circulation during pregnancy in future studies using MeD-seq.

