## 4. Study population

### 4.1 Population (base)

Placental samples will either be obtained via the Fetal Biobank Amsterdam (retrospectively), abortion clinics, including but potentially not limited to Gynaikon Kliniek Rotterdam and Bea & Bloemenhovekliniek (prospectively), and the Erasmus MC (both retrospectively and prospectively). The majority of first and second trimester samples from the Fetal Biobank Amsterdam and the Erasmus MC originate from pregnancies complicated by congenital defects or obstetric complications such as immature birth. Since, placental samples of uncomplicated pregnancies are needed as reference, first and second trimester samples from uncomplicated pregnancies terminated for social indications will be collected at abortion clinics. Third trimester placentas of both complicated and uncomplicated pregnancies will be collected at the Erasmus MC.

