### 4.2 Inclusion criteria

In order to be eligible to participate in this study, a subject must meet all of the following criteria:

- For samples retrospectively collected: residual placental tissue available at the Fetal Biobank Amsterdam or Erasmus MC from singleton pregnancy;

- For samples prospectively collected at the Erasmus MC or abortion clinic:
  - o Participant has to be at least 18 years of age
  - o Singleton pregnancy
  - o Participant is willing and able to give written informed consent
  - o Additional for abortion clinic: voluntarily chosen for elective, surgical abortion for social indication, before potential participation in this study is discussed.

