### For the prospective analyses:

For participants who will be recruited via an abortion clinic (first or second trimester) or at the Erasmus MC (first, second, or third trimester), informed consent will be asked before sample collection as described below. Patient information letters and informed consent forms are attached.

*9.2 If yes, please give a description of the recruitment and informed consent procedures. How and by whom (investigator, supervising doctor, other person) participants will be informed about the study and asked for their consent, how much time will they be given to consider the decision. The patient information letter with informed consent form should be attached as a separate document.*

Women enrolled at an abortion clinic will be informed about the possibility to participate in this study on a voluntary base after deciding for termination of the pregnancy. Study information will be given by an independent nurse or medical doctor working at the abortion clinic who is not involved in the study, as well as by the informed consent form. After informing about the study and asking informed consent, a potential participant can consider participating in this study until the surgical abortion takes place. Patient information letter and informed consent form are attached.

Women prospectively enrolled at the Erasmus MC in the first / second / third trimester will be informed about the possibility to participate in this study by a member of the research team and via the informed consent form. A potential participant can (re)consider participating in this study until the placenta is born. Patient information letter and informed consent form are attached.

*9.3 If no, exception consent: describe how it is safeguarded that subjects are excluded who have objected against the re-use of their data, human material, images.*

Potential participants recruited retrospectively at the Erasmus MC with known objection against material use for research according to the Erasmus MC "database bezwaren" will be excluded.

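### Sub-study 2: among uncomplicated pregnancies, collection route runs together with the first/second versus third trimester contrast, and no check for maternal DNA is stated before DMR calling

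*Protocol*

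**What the plan says.** All references are to the sub-study 2 protocol.

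- **Early reference tissue.** Section 4.1: "first and second trimester samples from uncomplicated pregnancies terminated for social indications will be collected at abortion clinics". Section 4.2 adds that an abortion-clinic participant must have "voluntarily chosen for elective, surgical abortion for social indication".
- **Other early tissue.** Section 4.1: "The majority of first and second trimester samples from the Fetal Biobank Amsterdam and the Erasmus MC originate from pregnancies complicated by congenital defects", or from obstetric complications. These samples therefore mostly do not supply the uncomplicated reference.
- **Late tissue.** Section 4.1: "Third trimester placentas of both complicated and uncomplicated pregnancies will be collected at the Erasmus MC". For prospective Erasmus MC participants, section 9.2 says "A potential participant can (re)consider participating in this study until the placenta is born", so that tissue is a delivered placenta.
- **Laboratory and analysis.** Section 5.1: "After sample collection, DNA will be isolated from placental biopsies". The read filter that follows separates methylation signal from background; it is not described as separating maternal from placental DNA. Testing is by chi-squared with FDR or Bonferroni correction.
- **Use of the result.** The primary objective is trimester-specific DMRs. Objective 3 reads "Identify placental DNA methylation profiles to specifically distinguish the placental derived fraction from the maternal one in total cfDNA".

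**The concern.** A placental sample may carry some maternal DNA from decidua or blood. How much could depend on how the tissue was obtained, and here that differs between early and late uncomplicated samples. A region that differs between mother and placenta would then differ between trimesters with no change in the placenta. Multiplicity correction limits chance findings. It does nothing about a systematic difference in tissue composition.

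Objective 3 is exposed in a second way. The profiles are to serve as the reference for telling placental from maternal cfDNA. Any maternal share in the reference tissue, even one equal in all trimesters, pulls the reference towards the maternal profile at the regions that are meant to separate the two.

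Later repair would be hard. Clinic and Fetal Biobank samples are anonymous (sections 10.1 and 11.3), and section 11.1 lists placental tissue only, so comparison with a maternal genotype is not provided for.

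**Working it through.** **No figure to reproduce.** Section 4.4 sets at least 10 samples per trimester from earlier MeD-seq experience and says power cannot be calculated. What follows is an illustration.

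**Inputs.** From the protocol: 10 samples per trimester and an adjusted significance level of 0.05. Assumed, because the protocol does not give them: maternal share *c*, placental methylation *P*, maternal methylation *M*, reads per window per sample, number of windows *m*, and pooling of reads over samples. Treating methylation as a proportion of reads is also a simplification.

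**Step 1: mixture.** Observed methylation = (1 − c)P + cM. With the same *P* in both trimesters, the apparent trimester difference is (c₁ − c₃)(M − P). It is zero when the shares are equal. For P = 0.10, M = 0.90 and shares 20% versus 5%:

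- early: 0.80 × 0.10 + 0.20 × 0.90 = 0.26
- late: 0.95 × 0.10 + 0.05 × 0.90 = 0.14
- difference: 0.15 × 0.80 = 0.12

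**Step 2: chance of a false DMR in one affected window.** Two-proportion test (the 2×2 chi-squared), n = 10 × reads per trimester, two-sided α = 0.05/m:

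z = [|p₁ − p₃|√n − z(α/2)·√(2p̄(1 − p̄))] / √(p₁(1 − p₁) + p₃(1 − p₃))

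Example at 100 reads, n = 1,000, m = 10,000: z(α/2) = 4.565 and p̄ = 0.20, so z = (3.795 − 4.565 × 0.566)/0.559 = 2.17, a chance of 98.5%.

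Results at m = 10,000:

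| P / M | Shares, early v late | Observed | 20 reads | 50 reads | 100 reads |
|---|---|---|---|---|---|
| 10% / 90% | 30% v 5% | 34.0% v 14.0% | 54.8% | 99.8% | >99.9% |
| 10% / 90% | 20% v 5% | 26.0% v 14.0% | 5.7% | 57.2% | 98.5% |
| 20% / 80% | 20% v 5% | 32.0% v 23.0% | 0.5% | 8.3% | 47.7% |
| 30% / 60% | 20% v 5% | 36.0% v 31.5% | <0.1% | 0.1% | 0.7% |
| 10% / 90% | 5% v 0% | 14.0% v 10.0% | <0.1% | 0.4% | 3.5% |

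At m = 1,000,000 the second row becomes 0.7%, 23.7% and 89.8%. With equal shares the rate stays at the nominal level.

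**Step 3: dilution of the reference.** The contrast between maternal and observed placental methylation is (1 − c)(M − P). For P = 0.20 and M = 0.80, a share of 5%, 10%, 20% or 30% cuts the 60-point contrast to 57, 54, 48 or 42 points. That is attenuation, not loss.

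**The case against.** The protocol misstates nothing here. Section 5.1 is a short answer on a review-committee form, and removal of maternal tissue may be set out in a laboratory procedure. The term biopsy itself suggests targeted sampling of placenta. This stands in part: the finding is that the protocol states no check, not that no separation will be done.

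Three stronger readings are tempting, and the protocol does not support them.

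- **All early tissue is surgical-abortion material.** It is not. Early samples also come from the Fetal Biobank and Erasmus MC, including spontaneous immature deliveries (section 9.1), and Erasmus MC recruits prospectively in all three trimesters (section 9.2). The overlap of route and trimester concerns uncomplicated samples, and only first/second versus third.
- **The maternal share does differ by trimester.** Nothing in the protocol says so, or describes the condition of clinic tissue or of delivered placentas. A difference by route is plausible but inferred.
- **The trimester contrasts should be re-ranked.** Making first versus second trimester primary, or accepting third-trimester DMRs only if they replicate there, would narrow the stated primary objective and could discard genuine late-gestation change. A shared route would not guarantee equal maternal shares in any case.

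It is also fair to say that new tissue-handling rules cannot reach stored samples, and that dropping outliers cannot correct a shift common to all early samples. The remedy therefore has to measure and report the signal, not only exclude samples.

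**Conclusion.** The point holds in a limited form. Among uncomplicated pregnancies the collection route coincides with first/second versus third trimester, and section 5.1 states nothing that would detect maternal DNA. Some trimester-specific DMRs could therefore reflect admixture, on condition that the maternal share differs by route. Dilution of the objective 3 reference does not need that condition; any maternal share is enough.

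The size cannot be derived from the protocol. Under the assumptions shown, the chance of a false DMR in an affected window runs from negligible to near-certain, driven by the gap in maternal share, the methylation contrast and the read depth. That spread is the reason to measure the maternal signal. It does not show that the results will be biased or that the design is unsound. This is a cheap improvement to make before DMR calling.

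**What to change.** In section 5.1, add a maternal-DNA check on the MeD-seq data, placed before DMR calling:

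1. In samples with Y-chromosome reads, estimate the maternal signal from methylated reads at X-linked CpG islands subject to X inactivation. A male placenta has a single X, so such reads point to maternal cells.
2. Report this signal by trimester and by collection route, and state how many samples could not be assessed.
3. Repeat the DMR analysis without clearly contaminated samples as a sensitivity analysis, with the cut-off written down beforehand.
4. Where the signal differs by trimester, describe first/second versus third trimester DMRs in uncomplicated pregnancies as possibly reflecting collection route.

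Keep the stated primary trimester contrasts.

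**Cost.** A small extra analysis on data already being generated, with no new samples. It is informative only in male pregnancies: if about half are male (assumed), roughly 5 of the minimum 10 samples per trimester. The estimate by trimester will be coarse, and samples without Y reads remain unassessed.

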**5.5 Medical device(s)/In vitro diagnostic tests:**

*Describe which medical device and/or in vitro diagnostic test is used, what the intended use of the medical device is and whether the medical device/diagnostic test is already available in the Erasmus MC.*

Not applicable.

**6. Unexpected discoveries**

**6.1 Is there a chance of unexpected discoveries?**

☐ Yes

☒ No

**6.2 If yes, describe the procedures, who will be notified, how the subjects are notified.**

**7. Exchange, sharing or transfer of data and/or human material and/or images outside Erasmus MC**

*Describe with which organization the data and/or human material and/or images are shared, are they profit or non-profit organizations, whether these organizations are in the EU or outside the EU, how the privacy of subjects is protected outside the Erasmus MC and describe the procedures regarding the exchange(s), whether a Data Transfer Agreement/Material Transfer Agreement is available (if yes, please upload the DTA/MTA).*

We will obtain placental samples via different Dutch abortion clinics and from the Fetal Biobank Amsterdam. All are non-profit organizations in the Netherlands. This data is only shared with us anonymously so subjects privacy is protected. We will not share the samples we obtained from the Fetal Biobank Amsterdam. For samples prospectively collected at an abortion clinic, informed consent to share data and/or placental tissues with third parties is asked in the informed consent form. However, at this moment there are no plans to share these tissues with other organizations outside the Erasmus MC.

## 8. Statistical analysis

### 8.1 Main study parameter/endpoint:

Trimester-specific DMRs in placental tissues of uncomplicated and complicated pregnancies using MeD-seq.

### 8.2 Secondary study parameters/endpoints:

Underlying genes or genetic pathways related to identified DMRs involved in (ab)normal placental development.

### 8.3 Other study parameters:

Identified placental DNA methylation profiles could contribute to specifically distinguish the placental derived fraction from the maternal one in total cfDNA in the maternal circulation during pregnancy in future studies using MeD-seq.

## 9. Recruitment and consent

### 9.1 Will the subjects be asked for informed consent?

- ☐ Yes (*Upload Patient Information Letter and Informed Consent*)
- ☐ No, only anonymous data is used, i.e. the data can never be traced back to an individual subject
- ☐ No, this research will be performed under the exception consent  
(*Upload form Care for data Template, in Dutch: Formulier uitzondering toestemming*)
- ☒ Other (e.g. partly, indirectly) *Please describe the situation.*

### For the retrospective analyses:

First and second trimester participants who will be recruited at the Fetal Biobank Amsterdam and third trimester participants who will be recruited at the Erasmus MC already provided informed consent for use of their residual placental material for (future) research (IC forms are attached).

First and second trimester participants who will be recruited at the Erasmus MC have not provided informed consent. However, since these pregnancies were mostly terminated because of congenital birth defects or spontaneous immature deliveries, it is emotionally undesirable to ask these patients in retrospect for informed consent to use residual placental material for this specific study. As part of regular care, pregnant women who visit the outpatient clinic of the obstetrics department have an appointment with a (research) nurse who, among others, discusses the potential use of residual material for research purposes. An information letter is also send to these women (see attached). Using an 'opting-out' system, only objection

against the use of residual material is registered in the patient record and in the 'database bezwaren'. We will limit the use of placental samples to women who have had an appointment with a (research) nurse during their pregnancy. Potential participants with known objection against material use for research according to the Erasmus MC "database bezwaren" will be excluded.

### For the prospective analyses:

For participants who will be recruited via an abortion clinic (first or second trimester) or at the Erasmus MC (first, second, or third trimester), informed consent will be asked before sample collection as described below. Patient information letters and informed consent forms are attached.

*9.2 If yes, please give a description of the recruitment and informed consent procedures. How and by whom (investigator, supervising doctor, other person) participants will be informed about the study and asked for their consent, how much time will they be given to consider the decision. The patient information letter with informed consent form should be attached as a separate document.*

Women enrolled at an abortion clinic will be informed about the possibility to participate in this study on a voluntary base after deciding for termination of the pregnancy. Study information will be given by an independent nurse or medical doctor working at the abortion clinic who is not involved in the study, as well as by the informed consent form. After informing about the study and asking informed consent, a potential participant can consider participating in this study until the surgical abortion takes place. Patient information letter and informed consent form are attached.

Women prospectively enrolled at the Erasmus MC in the first / second / third trimester will be informed about the possibility to participate in this study by a member of the research team and via the informed consent form. A potential participant can (re)consider participating in this study until the placenta is born. Patient information letter and informed consent form are attached.

*9.3 If no, exception consent: describe how it is safeguarded that subjects are excluded who have objected against the re-use of their data, human material, images.*

Potential participants recruited retrospectively at the Erasmus MC with known objection against material use for research according to the Erasmus MC "database bezwaren" will be excluded.

